## Abstract

**Background:**

Systemic ischemic-reperfusion injury following cardiac arrest results in multisystem organ failure, brain injury and death. The aim of this trial is to investigate whether the combined use of cortisol, ascorbic acid (vitamin C), and thiamine during the early post-resuscitation period reduces the neurologic injury among out-of-hospital cardiac arrest (OHCA) survivors treated with targeted temperature management (TTM).

**Method:**

This is a single-blind, multi-center, randomized, placebo-controlled trial to be conducted in nine tertiary university-affiliated hospitals in South Korea. A total of 160 OHCA survivors treated with TTM will be randomly assigned to the treatment or control groups (1:1 ratio). For the treatment group, patients will intravenously receive a combination dose of ascorbic acid (50 mg/kg, maximum single dose 3 g), thiamine (200 mg), and cortisol (100 mg) that will be mixed in three separate 50mL bags of 0.9% saline, respectively, every 12 hours for 3 days. For the placebo group, patients will receive three separate 50mL bags of 0.9% saline intravenously in the same manner. The primary outcome is the peak neuron-specific enolase level at 48–72 hours after the return of spontaneous circulation.

**Discussion:**

The potential benefits of ascorbic acid, thiamine, and cortisol as neuroprotective agents have been reported in previous preclinical trials. This trial is the first clinical trial to assess the neuroprotective effectiveness of a combination of ascorbic acid, thiamine, and cortisol for OHCA survivors.

**Trial registration:**

ClinicalTrials.gov NCT04921189

## Introduction

Cardiac arrest remains a significant global health challenge, with less than 8% of out-of-hospital cardiac arrest (OHCA) patients achieving favorable recoveries despite advancements in resuscitation medicine [1]. Systemic ischemic/reperfusion injury is a major injury mechanism in OHCA patients, which contributes to multiple organ failure, known as post-cardiac arrest syndrome [2,3]. Proposed mechanisms of injury include mitochondrial dysfunction, increased reactive oxygen species (ROS), metabolic disruption, the inflammatory cascade, and neuronal excitotoxic death, which persist after the return of spontaneous circulation (ROSC) [4,5]. Targeted temperature management (TTM) is the only established therapeutic method during the post-cardiac arrest period for comatose OHCA survivors [6,7]; however, additional pharmacological interventions to reduce the injuries could be beneficial.

Ascorbic acid (vitamin C), thiamine, and corticosteroids are known as potential therapeutic agents to alleviate ischemic/reperfusion injury after cardiac arrest [5]. Ascorbic acid acts as an antioxidant defense substance, reducing ROS and reactive nitrogen species and improving microcirculation by limiting oxidative injury and endothelial barrier disruption [8]. Thiamine is a key cofactor needed for pyruvate dehydrogenase function to resume aerobic metabolism and, therefore, to recover from mitochondrial dysfunction [9]. Corticosteroids can decrease the inflammatory response and improve microcirculatory flow [4,10]. It is also helpful to maintain hemodynamic stability for patients with post-arrest hypotension by enhancing vasopressor effects [11]. Theoretical and experimental studies suggested that the concomitant use of cortisol, thiamine, and ascorbic acid might have potential treatment synergism for whole-body ischemia/reperfusion injuries after cardiac arrest [12–14].

Many preclinical studies reported the beneficial effects of singular drugs such as thiamine, ascorbic acid, and corticosteroids in cardiac arrest animal models [9,15–17]; however, the limited human clinical trials have failed to show benefits [11,18]. The simultaneous occurrence of many dysregulated pathways during the post-cardiac arrest period necessitates the use of medications that can reduce the cascades of ischemic-reperfusion injury and successfully target the intended route [4]. The aim of this trial is to investigate whether the combined use of cortisol, ascorbic acid, and thiamine during the early post-resuscitation period would reduce neurologic injury among the OHCA survivors treated with TTM.

## Materials and methods

### Study design

The steroid, thiamine, and ascorbic acid during the post-resuscitation period for comatose OHCA survivors (STAR) trial is a single-blind, multicenter, randomized placebo-controlled trial being conducted in nine emergency departments (EDs) of tertiary university-affiliated hospitals in South Korea. The institutional review board of all participating hospitals have reviewed and approved the study protocol, including the institutional review board of Asan Medical Center (No. 2021–0613, approved on April 27, 2021). The STAR trial is registered under clinicaltrials.gov as protocol NCT04921189 on June 4, 2021. The study started on December 31, 2021 and the estimated study completion date is June 5, 2025. The investigators have obtained written informed consent from all patients’ legal surrogates. The Ministry of Food and Drug Safety in Korea has also approved the trial protocol. All OHCA survivors are being screened for eligibility by the attending emergency physician. Fig 1 shows the study schedule and Fig 2 illustrates the study flow chart.

**Fig 1 pone.0319733.g001:**
[figure not shown]
Data collection and follow-up of the participants in the STAR trial (SPIRIT figure). ROSC = Return of spontaneous circulation; SOFA = sequential organ failure assessment.

**Fig 2 pone.0319733.g002:**
[figure not shown]
Flow chart of the study protocol.

### Population

The study population will consist of adult patients (19–79 years old) with successfully resuscitated OHCA treated with TTM (target temperature between 32 and 36 °C). The patients over 79 years old were excluded due to the increased risk of comorbidities and frailty, which could confound the interpretation of neuroprotective effects and outcomes. The participating patients must meet all the inclusion criteria and none of the exclusion criteria (Table 1).

**Table 1 pone.0319733.t001:** Inclusion and exclusion criteria.

Inclusion criteria	Exclusion criteria
An out-of-hospital cardiac arrest survivors treated with targeted temperature management (target between 32 and 36 °C)	Patients who > 12 hours from cardiac arrest to drug or placebo administration
Cardiac arrest without obvious non-cardiac cause	Patients who have set limitations on treatment (e.g., patients with a signed do-not-resuscitate order), or with an underlying terminal-stage disease without an active treatment plan and those who are not expected to survive to discharge, or who are expected to die within 24 h despite best possible treatment, based on the judgement of medical personnel
	Patients taking at least 1 g/day of vitamin C or receiving intravenous thiamine prior to enrolment
	Known poor neurological status (Cerebral Performance Categories 3–5); glucose-6-phosphate dehydrogenase deficiency; pregnancy; thalassemia; hyperoxaluria; cystinuria; or ongoing gout attacks
	History of previous cardiac arrest, or oxalate renal stones
	Patients who do not voluntarily consent to participate in the trial (by legal proxy)

### Randomization, treatment allocation, and blinding

The patients will be randomly assigned in a 1:1 ratio to either the treatment group or the placebo group. The randomization sequence will be generated by *R* (version 3.3.3; R Foundation for Statistical Computing, Vienna, Austria; https://www.R-project.org) with randomized blocks of 4, stratified by recruitment site. The allocation sequence will be concealed from the attending emergency physicians and researchers enrolling and assessing patients in sequentially numbered, opaque, sealed, and stapled envelopes. The envelopes will be opened only at the allocation time. Given that patients are in a comatose state, they cannot perceive or differentiate the treatment solution from the placebo. To ensure blinding, study medications and placebo solutions are prepared by independent, unblinded personnel who are not involved in patient care or outcome assessments. However, the research team responsible for patient care and administering the treatments is aware of the group allocation. The primary outcome of this study, peak NSE levels at 48 and 72 hours after ROSC, is an objective biomarker, reducing the risk of bias associated with unblinded personnel. Additionally, secondary outcomes will be assessed by blinded evaluators to further minimize potential bias.

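### A single fixed block size of 4 within each site, with a care team that knows every allocation, lets up to about 30–33% of upcoming allocations be deduced: a preventable risk of selection bias

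*Protocol article*

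**What the plan says.** The section on randomization, treatment allocation and blinding in the protocol article fixes these elements:

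- A 1:1 ratio: "The patients will be randomly assigned in a 1:1 ratio to either the treatment group or the placebo group".
- One block size, applied per site: "with randomized blocks of 4, stratified by recruitment site". This describes random order within blocks of one size; no variation in size is mentioned.
- Concealment from the physicians and researchers who enrol and assess patients, by "sequentially numbered, opaque, sealed, and stapled envelopes. The envelopes will be opened only at the allocation time".
- Separate preparation: "study medications and placebo solutions are prepared by independent, unblinded personnel who are not involved in patient care or outcome assessments".
- Open allocation at the bedside: "However, the research team responsible for patient care and administering the treatments is aware of the group allocation".

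Three statements elsewhere bear on who could use this information. Under Study design: "All OHCA survivors are being screened for eligibility by the attending emergency physician". In Table 1, one exclusion rests on prognosis as judged by staff, covering patients "who are expected to die within 24 h despite best possible treatment, based on the judgement of medical personnel". Under Interventions, the randomization number is issued after surrogate consent, in order of enrolment, and attending emergency physicians also take treatment decisions during the trial. Under Trial status, recruitment is described as active, so the block size was published while patients were still being enrolled.

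**The concern.** Concealment needs the next assignment to be both hidden and unpredictable. The envelopes secure the first. A short block of fixed, known size undermines the second once earlier assignments at the site are known: after two like assignments the next two are determined, and the fourth in a block is always determined.

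The decision to enrol comes before the envelope is opened and includes a judgement about expected survival. Someone who could foresee the arm would therefore have room, even without intending it, to include or pass over a patient according to prognosis. The arms would then differ at baseline. The protections that the article names, an objective biomarker and blinded evaluators, act on how outcomes are measured. They do not correct a difference in who entered each arm, because peak NSE would faithfully record it.

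**Working it through.** **Inputs.** From the article: block size 4, ratio 1:1, stratified by site, nine sites, 160 patients. The article gives no figure for predictability, so there is none to reproduce. Its sample size does reproduce approximately: 2 × [119 × (1.960 + 0.842) / 57]² = 68.4 against the stated 68 per group, and 68 / 0.85 = 80, hence 160 in total.

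**Complete blocks of 4.** There are six equally likely orders of two treatment and two placebo assignments. An assignment is certain when one arm is already used up.

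| Position | Chance that it is certain | Chance that the best guess is right |
|---|---|---|
| 1 | 0 | 1/2 |
| 2 | 0 | 2/3 |
| 3 | 1/3 | 2/3 |
| 4 | 1 | 1 |

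Certain: (0 + 0 + 1/3 + 1) / 4 = 33.3%, or 0.333 × 160 = about 53 patients. Best guess: (0.500 + 0.667 + 0.667 + 1) / 4 = 70.8%.

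**Incomplete last blocks.** With near-equal sites (assumed: seven of 18 and two of 17, total 160), each site completes four blocks and leaves one or two patients in positions 1 and 2, where nothing is certain. Each site contributes 4 × 4/3 = 5.33 certain allocations. Nine sites give 48, and 48 / 160 = 30.0%. For an 18-patient site, best-guess accuracy is (16 × 0.7083 + 0.500 + 0.667) / 18 = 69.4%. With uneven site sizes drawn at random (2,000 draws, assumed), the share that is certain ran from 29.6% to 32.7%.

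**Varying the block size.** The last three rows simulate an 18-patient site (assumed; 5,000 runs). The observer knows the set of possible sizes and the full history, but not the size of each block.

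| Block sizes | Certain | Best guess right |
|---|---|---|
| 4 (exact) | 29.6% | 69.4% |
| 2, 4, 6 | 3.8% | 69.6% |
| 4, 6 | 5.8% | 68.4% |
| 4, 6, 8 | 2.3% | 66.9% |

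Varying the size removes nearly all certainty but little of the guessing advantage. Including size 2 leaves guessing no better than under fixed blocks of 4. A longer fixed block is not a substitute: size 6 still leaves 25% certain in complete blocks.

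**What selection could do (illustration; the shifts are assumptions).** Suppose that selection in the certain slots alone moved prognosis by d standard deviations, in opposite directions by arm. The spurious difference is 2 × d × 119 × (0.30 to 0.333).

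- d = 0.1: 7 to 8 units.
- d = 0.25: 18 to 20 units.
- d = 0.5: 36 to 40 units.

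The planned difference is 57 and the standard error is 119 × √(2/68) = 20.4. By the normal approximation, the two-sided type I error would rise from 5% to about 6–7%, 14–16% and 42–49% respectively.

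**The case against.** The strongest reply is that the well-informed enroller is inferred. The article says that the sequence is concealed from those who enrol, and says separately that the care team is aware of the arm. It nowhere states that these are the same people. This stands, and it makes the percentages a worst case: they need someone who knows the block size, the complete site history and the current position in the block. Overlap is nevertheless likely, because attending emergency physicians both screen patients and direct treatment.

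Recruitment is also slow. About 160 / 9 = 18 patients per site over some 41 months (December 2021 to June 2025) is one patient roughly every two months, or somewhat more often if enrolment stops early for follow-up. Keeping track of a block over such gaps takes effort. This lowers the likelihood but does not remove the possibility.

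The Statistical analyses section adjusts for age, sex, initial rhythm, collapse time, underlying disease and a severity grade, particularly if imbalances are seen, with site as a random effect. That handles measured severity. It does not reach features that a clinician sees at the bedside and the case report form does not capture.

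Finally, the trial openly declares itself single-blind. A reader might infer that blinded preparation combined with an informed bedside team is an error that defeats the design. The documents do not support that reading: the level of blinding is declared, and the open allocation is disclosed. Treatment and care after allocation are a separate matter, which a change of block size would not affect.

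**Conclusion.** The point holds as a weakness in how allocation is protected. With one fixed, published block size per site and known past assignments, up to about 30–33% of allocations (48–53 of 160) could be deduced with certainty and about 69–71% guessed correctly. The upper figures apply only if every block is completed; with nine near-equal sites the values are 30% and about 69%. The result rests on an enroller who knows the block size and the site's history, which the article makes likely but does not establish.

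A reader might go further and infer that concealment has failed, or that enrolment has been steered. Nothing in the article shows either, and the bias figures above are illustrations of vulnerability, not estimates. This is a preventable risk with a cheap remedy, and it does not by itself invalidate the trial.

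**What to change.** 1. For all remaining allocations, generate new site lists with randomly varying block sizes, for example 4, 6 and 8 rather than 2, 4 and 6. Hold the lists only at the coordinating centre and do not disclose the sizes to sites. On the simulation above, this takes certain allocations from about 30% to about 2%, and best-guess accuracy only to about 67%.
2. Because any guess depends on known past assignments, where feasible have the existing independent preparers release covered bags labelled by study number, so that enrolling and bedside staff are not told the arm. This is secondary: it changes the declared level of blinding.
3. For patients already enrolled, compare baseline severity by arm and by position in the block, looking in particular at the third and fourth positions. This needs no operational change and remains useful if few slots are left, a number that the article does not give.

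Cost: new lists and envelopes, bag covers if step 2 is adopted, and a minor amendment. The possible imbalance within a site grows slightly, from at most 2 patients (half a block of 4) to at most 4 (half a block of 8).

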### Interventions

As soon as possible after achieving ROSC at the ED or arrival after achieving ROSC before ED admission, patients who meet inclusion criteria will be identified. After written consent is obtained from legal surrogates, a unique randomization number will be allocated to each participant in the order of enrolment. For the treatment group, ascorbic acid (50 mg/kg, maximum single dose 3 g, daily dose 6 g), thiamine (200 mg, daily dose 400 mg), and corticosteroid (100 mg, daily dose 200 mg) will be mixed in three separate 50mL bags of 0.9% saline, respectively, and administered through intravenous infusion over 60 min every 12 h for 3 days. For the placebo group, an identical volume of 0.9% saline (50 mL, respectively) will be administered through intravenous infusion over 60 min every 12 h for 3 days. The first administration of the study medication is aimed as soon as possible after ROSC, at least not to delay over 12 hours after ROSC.

All the participants will be treated with post-resuscitation care in accordance with the current guidelines [6,19,20]. Depending on the attending emergency physicians’ decision, in case of clinically suspected vitamin C, thiamine, or adrenal insufficiency, supplementation of ascorbic acid, thiamine, or corticosteroids is permitted. For patients requiring high dose vasopressors, corticosteroid administration is permitted based on the attending physician’s judgment. If the legal proxy requests withdrawal from the trial, the collected data and blood samples will be removed.

### Data collection

T_ROSC24_, T_ROSC48_, and T_ROSC72_ indicate the time points of 24, 48, and 72 hours after ROSC, respectively. T_0_ is the time point of the first drug administration, which will aim to be administered within 12 hours after ROSC. The patients will receive the medication every 12 hours after T_0_, six times. T_ROSC24_ is between T_12_ and T_24._ Blood samples for plasma ascorbic acid and thiamine levels will be collected at enrolment prior to study drug administration and 72 hours after ROSC which will be transferred to the central laboratory for analysis. Blood samples for neuron-specific enolase (NSE) levels will be collected at 24, 48, and 72 hours after ROSC, and analyzed at the local laboratory of each participating hospital. A laboratory medicine specialist in all participating academic hospitals will assess the hemolysis index before reporting NSE values to ensure accurate NSE levels. Other blood samples will be collected at enrolment prior to study drug administration and daily for 3 days. We plan to collect and store serum samples at the same time, which will be frozen at -80°C immediately for future biomarker analysis. Adverse events and survival data will be monitored daily during hospitalization. The investigators will be blinded to the study group assignments and will conduct follow-up telephonic interviews for survival and neurocognitive function after hospital discharge around days 30, 90, 180, and 365.

An independent monitoring officer at the coordinating center will monitor the study procedures and data quality according to the Korea Good Clinical Practice guidelines in all participating centers. All data will be anonymized and collected using standard clinical report forms by investigators at each participating hospital. The monitoring officer will review and verify all data from inclusion to follow-up. The data will be stored at the coordinating center.

### Outcome measure

The primary outcome will be the peak NSE level at 48 or 72 hours after ROSC. If a patient dies before 48 hours, the patient will be excluded from the primary analysis. If a patient dies between 48 and 72 hours after ROSC, the NSE level at 48 hours will be used. Secondary outcomes will include as follows: ΔNSE level, Δ sequential organ failure assessment (SOFA) score, mortality (7-day, 30-day, 90-day, 180-day, in-hospital), time to death (days), length of intensive care unit (ICU) stays (days, up to 1 year), length of hospital stays (days, up to 1 year), ICU-free days within 14 days, time to awakening (days to neurological recovery, defined as Glasgow coma scale >13 after ROSC) and neurological outcomes (30-day, 90-day, 180-day). The ΔNSE level is the serial change in NSE level that reflects the severity of reperfusion injury during the post-cardiac arrest period (ΔNSE level = the peak NSE level at 48 and 72 hours after ROSC NSE level at 24 hours after ROSC). The Δ SOFA score is defined as the difference between the SOFA score at enrolment and the maximum SOFA score between 24 and 72 hours after ROSC (ΔSOFA score = initial SOFA score at enrolment − maximum SOFA score between 24 and 72 hours after ROSC). If a patient dies in the first 72 hours, the maximum SOFA score will be counted as 24. Neurological outcomes will be assessed using cerebral performance category scores and the modified Rankin scale at 30, 90, and 180 days after ROSC. A good neurologic outcome is defined as cerebral performance category scores of 1–2 and modified Rankin scale of 0–2, respectively.

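### ΔSOFA gives early deaths different scores according to entry severity, and ΔNSE starts from a value taken on treatment: both exploratory outcomes are hard to interpret, and cheap to clarify

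*Protocol article*

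**What the plan says.** Under Outcome measure, the protocol article lists ΔNSE and ΔSOFA as the first two secondary outcomes.

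- **ΔSOFA** is given as a formula: "ΔSOFA score = initial SOFA score at enrolment − maximum SOFA score between 24 and 72 hours after ROSC". A more negative value is worse. For early deaths the rule is "If a patient dies in the first 72 hours, the maximum SOFA score will be counted as 24"; enrolment SOFA is still subtracted.
- **ΔNSE** is described thus: "The ΔNSE level is the serial change in NSE level that reflects the severity of reperfusion injury during the post-cardiac arrest period". The bracketed formula sets the 48/72-hour peak against the 24-hour value. The operator between them is lost in the text at hand, and I read it as a minus sign. The lost symbol is not an error in the plan.
- **Timing** (Data collection): the first dose is one "which will aim to be administered within 12 hours after ROSC", with further doses every 12 hours, six in all. The 24-hour time point after ROSC is placed between 12 and 24 hours after the first dose. For NSE, "Blood samples for neuron-specific enolase (NSE) levels will be collected at 24, 48, and 72 hours after ROSC"; no pre-dose NSE sample is listed.
- **Analysis** (Statistical analyses): primary and secondary outcomes go into mixed-effects models with site as a random effect. The fixed covariates are given as examples and tied in part to observed imbalance. Enrolment SOFA is not among those named.
- **Status** (Discussion): secondary outcomes are to be treated as exploratory.

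**The concern.** Counting a death as 24 is presumably meant to make death the worst result. Subtracting a varying enrolment score undoes this: deaths no longer share one value, the sicker of two patients who die gets the better score, and some survivors rank below some deaths. A mean ΔSOFA then mixes entry severity with what happened afterwards.

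ΔNSE has a different difficulty. Its starting value is measured after randomisation and after treatment has begun. A reader who takes it for change from baseline would understate the drug's effect on NSE if part of that effect had appeared by 24 hours. The trial's rationale is early treatment, so this misreading is likely. The Discussion presents the trial as preliminary information for later work, so a misread secondary result could carry forward.

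**Working it through.** **The plan's own figures.** The sample size concerns peak NSE only: mean 114, SD 119, a 50% reduction (difference 57), 80% power, two-sided 0.05. The formula gives 2 × [119 × (1.960 + 0.842) / 57]² = 68.4 per group, in line with the stated 68; 68 / 0.85 = 80. Neither change score enters this calculation.

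**ΔSOFA, ordering.** Let b be enrolment SOFA and M the maximum at 24 to 72 hours. A survivor scores b − M and a death scores b − 24.

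| Patient | Enrolment | Maximum used | ΔSOFA |
|---|---|---|---|
| Dies | 16 | 24 | −8 |
| Dies | 14 | 24 | −10 |
| Dies | 8 | 24 | −16 |
| Survives | 4 | 15 | −11 |

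A survivor ranks below a death whenever the survivor's rise exceeds 24 minus the dead patient's enrolment score. On an assumed uniform grid (enrolment 6 to 16, survivor maximum 6 to 20), 56 of 1,815 combinations (3.1%) reverse the order and 28 tie. Reversals are possible but not the rule. The dependence of a death's score on entry severity affects every early death.

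**ΔSOFA, bias.** Enrolment SOFA precedes treatment, so its expectation is the same in both arms. The expected arm difference in b − M is therefore minus the expected arm difference in M with death = 24. There is no bias.

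**ΔSOFA, precision.** Let r be the correlation of b with M, and k = SD(M) / SD(b). The variance of the adjusted analysis relative to the change score is

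k²(1 − r²) / (1 + k² − 2rk).

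The denominator minus the numerator is (1 − rk)², which is never negative. Apart from the single degree of freedom for the covariate, the change score is thus never more precise, and the two are equal only when rk = 1.

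- Equal SDs (k = 1): the ratio is (1 + r)/2, a reduction of 40% at r = 0.2 and 20% at r = 0.6.
- Deaths coded 24 widen the spread of M. Assume enrolment SD 3, survivor maximum with mean 11 and SD 3, and 15% deaths. Then Var(M) = 0.85 × 9 + 0.85 × 0.15 × 13² = 29.2, SD 5.4, and k = 5.4 / 3 = 1.8. The reduction is about 12%, 3% and 0.3% at r = 0.2, 0.4 and 0.6.

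The article gives no SOFA SD, correlation or early death rate, so all of these inputs are assumptions.

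**ΔNSE, timing.** If the first dose is given less than 12 hours after ROSC, two doses have started before the 24-hour sample. If it is given at exactly 12 hours, one has been given and the second falls due at 24 hours. The 24-hour value is on treatment in every case that keeps to the plan.

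**ΔNSE, size.** With planned peak means of 114 and 57, the arm difference in ΔNSE is 57 minus the arm difference already present at 24 hours. The control 24-hour mean is not given; I assume 40, 60 or 80.

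| Assumed control 24-h mean | No effect at 24 h | 24-h value also halved |
|---|---|---|
| 40 | 57 | 57 − 20 = 37 |
| 60 | 57 | 57 − 30 = 27 |
| 80 | 57 | 57 − 40 = 17 |

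In the right-hand column the relative effect is unchanged. At 60, for example, ΔNSE is 54 in controls and 27 on treatment, still a halving.

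**The case against.** The case for leaving both outcomes alone is substantial, and much of it stands.

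- **ΔSOFA.** The planned models compare means, not ranks, and randomisation balances enrolment SOFA in expectation. At any given enrolment score, no survivor can score below a death. A reader might infer that ΔSOFA rewards deaths among the sickest, or favours an arm in which they die. The documents do not support that: no patient scores better by dying, and the mean comparison is unbiased.
- **Precision.** A reader might also expect a firm 20 to 40% gain from adjustment. That needs equal variances, which the death coding itself makes doubtful.
- **Covariates.** The named covariates are only examples, so enrolment SOFA could still be added. In a linear model of ΔSOFA it would give the same treatment estimate, with the sign reversed, as modelling maximum SOFA. This shows how small the change is, but the article does not commit to it.
- **ΔNSE.** The article never calls the 24-hour value a baseline, and the rise from 24 hours to the peak is a legitimate quantity. An early effect that lasts to 48 or 72 hours is captured by the primary outcome, so the trial does not lose it. A smaller difference in ng/mL does not by itself show lost power, because subtracting a correlated value also changes the SD.

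What remains is interpretation: a death score that varies with entry severity, and a change measure that is easily taken for the whole effect.

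**Conclusion.** The point holds as a minor one. ΔSOFA gives deaths unequal values and can place a survivor below a death. The randomised mean difference is unbiased, but the unadjusted score is hard to interpret and no more precise than an adjusted one. The variance reduction from adjustment runs from near 0 to about 40% over r = 0.2 to 0.6 and SD ratios of 1 and about 1.8, all assumed.

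ΔNSE measures the later, on-treatment rise and excludes any effect present by 24 hours. How much that is cannot be known from the article, which gives no 24-hour NSE. A reader might conclude that ΔNSE would vanish if the drug worked early. That would require the absolute reduction at 24 hours to equal the full reduction at the peak, and nothing in the article indicates this.

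It would go too far to call either outcome invalid. The primary outcome and sample size are untouched, and both measures are declared exploratory.

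**What to change.** 1. **SOFA.** Analyse the maximum SOFA at 24 to 72 hours, with death in the first 72 hours counted as 24, in the planned mixed model with enrolment SOFA as a prespecified fixed covariate, whether or not the arms look imbalanced. Every early death then has the same outcome value.
2. **NSE.** Keep ΔNSE if the later rise is of interest, but state that it starts from an on-treatment value and is neither change from baseline nor the total effect on NSE. Report the arm differences at 24, 48 and 72 hours beside it, for example from a mixed model of log NSE with treatment-by-time terms. Moving to the log model is partly a choice of what to estimate, so it supplements ΔNSE and is not a correction of it.

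The cost is a change of analysis wording, best made before any unblinded analysis. Enrolment SOFA and all three NSE samples are already collected, and sample size and trial conduct are unaffected.
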